#### Mixed Methods

This research will use an embedded mixed methods design [23] because both quantitative and qualitative dyadic data about the acceptability of the intervention will be collected. In this case, a qualitative strand has been added within a primarily quantitative-focused design (trial assessments and paradata) to enhance our understanding of what participants and couples liked and disliked about the intervention and to provide context about why they appreciated certain features, and, if applicable, what things they wished the intervention had but did not. Put simply, this research will review the findings obtained from analysis of the quantitative data and paradata along with the findings from the qualitative analyses to provide a more comprehensive picture about participants’ and couples’ use and thoughts of P3 relative to their relationships and managing their vulnerability to HIV and other STIs.

#### Aim 3: Preliminary Efficacy of the Intervention

Using the 6-month pilot RCT, this research will examine the preliminary efficacy of the intervention on couples: (A) formation and adherence to an HIV and STI prevention care plan containing evidence-based strategies (eg, ART for U=U, PrEP, and routine testing); (B) formation and adherence to a detailed sexual agreement, (C) relationship functioning (eg, mutual constructive communication and self-efficacy of decision-making and working together), and (D) self-reported and biomarker-confirmed indicators of vulnerability vis-à-vis sexual behaviors (eg, CAS) and HIV and STIs. The pilot RCT will have an allocation ratio of 1:1 and block randomization with a block size of 2, with blocks defined by dyad serostatus. Outcomes A and B will be dichotomous, outcome C will be continuous based on a bounded Likert scales, whereas outcome D will be a count variable based on STI incidence, HIV incidence, and CAS.

Preliminary efficacy will be assessed by considering changes in couples’ outcomes A to D over time. For the immediate intervention arm, the differences in outcomes A to D will be observed between receipt of the intervention and subsequent follow-up assessments at 3 months and 6 months (n=30). For the waitlist arm, the differences in outcomes A to D will be observed between receipt of the intervention after the 3-month assessment and subsequent follow-up assessment at month 6 (n=30). As such, this study will be able to pool and combine data from the 30 couples from the immediate intervention arm with data from the 30 couples from the waitlist arm to observe changes in outcomes (ie, from A-D) over a 3-month time period (N=60). Furthermore, through this study, we will also be able to observe changes in couples’ outcomes (ie, from A-D) for a longer period of time (6 months) for the immediate intervention arm (n=30). Comparisons in couples’ outcomes A to D by trial arm (immediate arm vs waitlist arm) will occur between baseline and month 3. In summary, the design we chose for the proposed 6-month pilot RCT is advantageous for 3 reasons: (1) it will allow us to compare differences between immediate intervention and delayed intervention arms for 3 months; (2) it will allow us to make comparisons within the delayed arm from no intervention before to intervention after (months 3 to 6) the assessment; and (3) it will facilitate generating additional intervention data that can be pooled from the immediate and delayed intervention arms to obtain more robust estimates of intervention effect size to more accurately estimate sample size and power for an efficacy RCT in the future.

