**Figure 2 figure2:**
[figure not shown]
Para Ti, Para Mí, Para Nosotros (P3) web app landing page to access the eligibility screener and the intervention via an “iniciar session.”.

In addition to a secure SMS text messaging system to communicate with participants, the P3 DHI also contains an administrative and clinical portal for researchers and staff. The administrative portal serves as a one-stop shop to store, organize, and monitor data associated with the trial. Along with its other features, the portal contains a dashboard and participant tracking system. The dashboard provides a global overview of all study participants and couples’ engagement with the study, ranging from data associated with eligibility and enrollment rates and information on assessment and module completions. The dashboard also offers researchers and staff the ability to download data about participants’ and couples’ experiences with regard to using the intervention modules within the P3 DHI. Finally, as each couple progresses through the trial, the participant tracking system provides descriptive details including due and completion dates of assessments as well as when and which modules are completed.

Both the dashboard and participant tracking system are interactive such that all numbers displayed in the dashboard provide the administrative user the ability to learn more about which specific participants or couples are linked to a particular characteristic in the dashboard (eg, number of enrolled couples in the immediate intervention arm). In addition, each participant and couple are assigned a unique ID. Selecting and clicking on the unique ID in the administrative portal leads to a web page providing information about the couple, their assessments (eg, due date and completion date), their module use (date of completion relative to assessment timeline for trial), links to their screener responses, when and which SMS text message reminders they have received, contact information, and HIV and STI testing details, including results. Figures 3 and 4 provide screenshot examples of the administrative portal.

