#### Level 3: Study Onboarding Zoom Meeting

Couples who meet all eligible criteria, provide e-consent, enter complete and accurate contact information, and pass the requirements for *relationship verification and data validation* will be invited to partake in a 10 to 15-minute onboarding Zoom meeting. During the meeting, the study staff will assess the couples’ verification and interest in participating, discuss study expectations and timelines, answer questions, and decide whether to admit the couple into the study. Once admitted, each partner of the couple will be asked to create their own profile on the P3 DHI using their own web-connected device. Their profile will give them access to the baseline assessment followed by whichever intervention group they are randomly assigned to for the pilot RCT.

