### Randomization

An allocated randomization block of 2:2, via an embedded algorithm within the P3 DHI, will be used to randomly assign couples to one of the following 2 intervention conditions following the baseline assessment: (1) an immediate intervention condition where couples will be able to use the P3 DHI for 6 months or (2) a 3-month delayed intervention condition where couples will be able to use the P3 DHI for the last 3 months of the trial. For ethical reasons, a delayed control condition was chosen for the trial study to provide all couples with access to the intervention while also permitting the ability to compare outcome differences between trial arms for the first 3 months of the pilot RCT. In sum, all couples in the pilot RCT will have access to use the P3 DHI for a minimum of 3 months, which will enable data pooling of the entire couple sample (N=60; ie, first 3 months for the immediate intervention condition plus the last 3 months with the delayed intervention condition). The study design will also enable the examination of long-term effects of the P3 DHI (ie, effects after 6 months of use) on outcomes and their use of the P3 DHI among couples randomized to the immediate intervention condition (n=30). Randomization will be blinded to couples but not to the study staff (administrators).

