### Pilot RCT Baseline and Follow-Up Measures

Items about evaluation will only be assessed during follow-ups after the participants receive the intervention. All other measures, items, and scales will be assessed at each time point throughout the trial, including baseline. In addition to screening for inclusion, the eligibility screener will capture a variety of demographic information from each participant including age, race, sex at birth, gender identity, sexual identity, highest education attainment, current employment status, has a primary health care provider, relationship type, relationship length, couple cohabitation, and couple HIV serostatus. Other demographic information will be captured at each data collection time point (ie, at baseline, months 3 and 6) to assess participant’s current living arrangement, type of health insurance, affordability to pay for health care or medication costs when needed in the past 3 months, as well as whether participants were in a situation that required them to reduce a meal size or skip a meal because of not having enough money for food in the past 3 months (social determinants of health). Skip patterns will be used accordingly for baseline and follow-up assessments at months 3 and 6. Multimedia Appendix 1 [24,27-49] provides a brief description of all other items and scales that will be assessed at each time point and how they relate to the constructs of CIT-HBC [13,14].

Beyond the General Anxiety Disorder 2-item, 5 other items will be used to capture aspects about anxiety and worry specifically related to sex and being in a relationship. The items include the following: “Do you ever feel like you are walking on eggshells around your partner? (Yes, No, I don’t remember)”; “In thinking about the past 3 months, how much did you worry or feel anxious about having sex with your partner? (0=never to 4=always)”; “To what extent did this anxiety stop you from enjoying sex with your partner? (0=not at all to 2=a lot)”; “In thinking about the past 3 months, how much did you worry or feel anxious about having sex with others, not including your partner? (0=never to 4=always)”; and “To what extent did this anxiety stop you from enjoying sex with others, not including your partner? (0=not at all to 2=a lot).” Skip patterns will be used for the above set of items such that some items may not be displayed depending on the participant’s response to the previous item.

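### Block size is given as 2 in one section and 2:2 in another; either leaves allocations open to prediction by unblinded staff, and the primary chi-square ignores the blocking factor

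*Protocol article*

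**What the plan says.** The Aim 3 section sets a 1:1 ratio and "block randomization with a block size of 2, with blocks defined by dyad serostatus". The Randomization section describes the same step as "An allocated randomization block of 2:2, via an embedded algorithm within the P3 DHI" and mentions no strata there, although the Trial Study Design section plans 10 couples per serostatus group in each arm.

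On who knows what, and when:

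- Randomization section: "Randomization will be blinded to couples but not to the study staff (administrators". Allocation follows the baseline assessment.
- P3 User Interface and User Experience section: a portal user can open any dashboard count to see the couples behind it. The example given is "number of enrolled couples in the immediate intervention arm".
- Pilot RCT Baseline and Follow-Up Measures section: the eligibility screener already collects "relationship length, couple cohabitation, and couple HIV serostatus", so the stratum is known before allocation.
- Level 3 section: at the onboarding meeting study staff "answer questions, and decide whether to admit the couple into the study". Each admitted partner then creates a profile and reaches the baseline assessment.

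The Primary Analyses section compares the arms on outcomes A, B and D with a one-degree-of-freedom chi-square in a univariate analysis. The Results section reports 74 couples enrolled, data collection ended in April 2024, and analysis in progress.

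**The concern.** Two things look wrong. First, the two descriptions of the block do not agree. If 2:2 lists the contents of a block, its size is 4; if it is a loose way of writing 1:1, it does not give the size stated under Aim 3.

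Second, a short fixed block combined with visible assignments can be worked out. In a block of 2, once the first couple in a serostatus group is allocated, the second couple's arm is settled. The embedded algorithm protects how the sequence is generated, but not against someone deducing the next arm from earlier ones on the dashboard. A person who could do that and also had a say in admission could admit, delay or discourage couples accordingly, even without intending to. Intention-to-treat analysis does not undo selection that takes place before randomisation, and the chi-square planned for A, B and D uses neither the blocking factor nor the baseline values. At stake are the month-3 arm comparison and the effect sizes that the pilot is meant to pass on to an efficacy trial.

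**Working it through.** **Inputs.** Three serostatus groups with 10 couples per arm in each (Trial Study Design); block of 2 (Aim 3) or 2:2 (Randomization); 74 couples enrolled (Results).

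**Planned total.** 3 × 2 × 10 = 60, which matches the stated sample. Each stratum of 20 would hold 20/2 = 10 blocks of 2, or 20/4 = 5 blocks of 4.

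**Rule.** An allocation is certain when one arm of the current block is already full. The best guess is the arm with more places left, or a coin toss when they are equal. The observer is assumed to know the block size and the earlier arms in the stratum.

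**Block of 2**
- Certain: second position only, 1/2 = 50%.
- Correct guesses: (1/2 + 1)/2 = 75%.

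**Block of 4**
- Certain: position 4 always; position 3 when the first two were alike (probability 1/3). (1/3 + 1)/4 = 33.3%.
- Correct guesses by position: 1/2; 2/3; (1/3 × 1) + (2/3 × 1/2) = 2/3; 1. (1/2 + 2/3 + 2/3 + 1)/4 = 70.8%.

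| Block | Certain at randomisation | Of 60 | Of 74 | Best guess right |
|---|---|---|---|---|
| 2 | 50% | 30 | 37 | 75% |
| 4 | 33.3% | 20 | 24.7 | 70.8% |

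Full enumeration of all balanced sequences gives the same values. The counts treat all blocks as complete. With blocks of 2 and 74 couples in three strata, either no stratum or two strata have an odd size, so the count is 37 or 36.

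**From randomisation back to admission.** The order is: screener, onboarding and admission, profile, baseline assessment, automated allocation. A forecast made at admission is certain only if no other couple of the same serostatus is randomised before this couple completes baseline. The table is therefore an upper bound at the one point where staff are described as making a decision.

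**What a check on the data could detect.** Assume blocks of 2, equal arms and complete data. The probability p of immediate allocation implied by earlier allocations is then 0.5 for half the couples, 0 for a quarter and 1 for a quarter.
- Baseline characteristic on p alone: variance of p = 0.5 × 0.25 = 0.125; SE = SD/√(74 × 0.125) = 0.33 SD. With 80% power at two-sided 5%, the detectable gap between p = 0 and p = 1 is 2.8 × 0.33 = 0.92 SD.
- Month-3 outcome on p and arm: within an arm p takes two values 0.5 apart, so its variance is 0.25² = 0.0625; SE = SD/√(74 × 0.0625) = 0.465 SD; detectable gap 2.8 × 0.465 = 1.30 SD.

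Only gross selection would show.

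**The case against.** The strongest reply is that the predictability figures belong to a moment at which nobody decides anything. Staff judgement is exercised at onboarding, while allocation is automated and depends on when both partners finish baseline on their own devices. That stands, and it is why the figures are upper bounds.

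A reader might infer that the people admitting couples could see the arms and knew the next one. The article does not support this. It says study staff in both places, but not that the same individuals do both tasks, nor that they knew the block size. An article may leave role separation to the full protocol or operating procedures, so silence on it is not a fault. Nor does the article show that any selection took place.

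Other points carry some weight. Levels 1 and 2 of eligibility are decided by algorithm, and level 3 is largely verification, so discretion is narrow, though not absent. Every couple receives P3 within the trial, which weakens any motive to steer. Reliance on self-reported outcomes concerns response bias and does not make this problem worse. Small blocks serve the target of 10 couples per serostatus group per arm, but blocks of 4 would divide a planned stratum of 20 evenly too. The trial is a pilot powered only for large effects. Finally, analysis changes made now come after data collection, and adjustment cannot remove selection on unmeasured traits.

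None of this settles which block was used, or explains why the primary test leaves out the factor that defined the blocks.

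**Conclusion.** The point holds in a limited form. The two block descriptions conflict and must be reconciled to what the app was programmed to do. Under either description, allocations are open to prediction by anyone who sees earlier arms and knows the block: up to 50% certain and 75% guessable with blocks of 2 (36 or 37 of 74 couples), or 33% and 71% with blocks of 4. These figures assume fixed blocks and full knowledge of earlier arms in the stratum, and they apply at the moment of randomisation; at admission the true share is lower by an amount the article does not allow one to compute.

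This is a vulnerability, not evidence of bias, and the documents give no basis for sizing a bias. It deserves action now because data are still being analysed, and because a univariate chi-square for A, B and D sets aside both the serostatus blocking and baseline information already collected.

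**What to change.** 1. State the block size and strata actually programmed, and make the Randomization and Aim 3 sections agree. Cost: a text correction after checking the app's settings.
2. Replace or supplement the univariate chi-square for A, B and D with an analysis stratified by, or adjusted for, dyad serostatus and the baseline value of the outcome. Label it as specified after data collection ended, and show the unadjusted result beside it. Cost: one further model per outcome on existing data.
3. Add a sensitivity check relating baseline characteristics, and month-3 outcomes given arm, to the allocation probability implied by earlier allocations in the same stratum. HIV and STI tests are done only at baseline and month 6, so the month-3 part covers self-reported outcomes. State its low power at 74 couples, and do not read a null result as reassurance. Cost: one analysis, provided the app recorded allocation order.
4. Report possible predictability as a limitation, saying which staff could see arms and whether they took part in admission.

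Enrolment has ended, so changing the block scheme cannot help this trial. Randomly varying block sizes and hiding arms from admitting staff are recommendations for the later efficacy RCT.

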### Specific Aims

There are 3 specific aims for this pilot RCT with adult cisgender SMM couples in Lima, Peru:

To assess the feasibility of retaining 60 eligible couples who consented to participate in a 6-month pilot RCT, through quantitative measurement of enrollment, retention, and attrition rates plus reason(s) for attrition.To describe the acceptability of P3 using mixed methods [23] from 3 data sources: at final follow-up, the partners’ responses to the Health Information Usability Evaluation Scale [24] and other survey items (eg, 3 things liked best or least about P3 and features for improvement) will be captured, along with the additional details they will share about their experiences during the individual-level, qualitative exit interview. Partners’ paradata will also be descriptively analyzed to describe the patterns of use, such as completion rates, time, and reuse.To examine the preliminary efficacy of the P3 DHI on couples through the following measures:Formation and adherence to an HIV and STI prevention care plan containing evidence-based strategies (eg, using ART for undetectable=untransmissible [U=U], PrEP, and routine testing)Formation and adherence to a detailed sexual agreementRelationship functioning (eg, mutual constructive communication, self-efficacy of decision-making, and working together)Self-reported and biomarker-confirmed indicators of vulnerability vis-à-vis sexual behaviors (eg, condomless anal sex [CAS]) and HIV and STIs

To accomplish the above specific aims, data will be collected from both the partners of the couple during the trial; analytic comparisons will be made between the 2 intervention trial conditions. The purpose of this paper is to describe the protocol that will be used to conduct a 6-month pilot RCT of the P3 DHI with adult cisgender SMM couples in Lima, Peru.

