## Methods

### Trial Study Design

The study design for the P3 DHI is a 6-month pilot RCT with an unmatched delayed control condition of 3 months. The pilot RCT for the P3 DHI is registered on ClinicalTrials.gov (NCT05873855). Assessments will occur every 3 months after the baseline assessment (at 3 and 6 months). Participants (ie, couples) will initially be blinded to which randomized condition they receive for the pilot RCT. Most study participation activities, including recruitment, eligibility screening, consent, enrollment, assessments, intervention, and exit interviews will occur on Zoom (Zoom Video Communications). During the pilot trial, participants will also undergo in-person HIV and STI testing at a local community-based organization at baseline and month 6. The planned sample size for enrollment is 60 adult cisgender SMM couples. The planned sample size will be balanced by dyad HIV serostatus and stratified by trial arm (ie, 10 seroconcordant negative, 10 serodiscordant, and 10 seroconcordant positive couples per arm). Florida International University (FIU) and Universidad Peruana Cayetano Heredia’s respective institutional review boards have approved the study protocol and all associated study activities.

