Furthermore, some scales will be modified based on feedback from the Community Advisory Board and to help reduce time burden for participants. For instance, single global items from validated scales (eg, Dyadic Trust Scale [34] and Investment Model short form [36]) may alternatively be used to capture interpersonal trust, relationship commitment, and relationship satisfaction instead of the complete scale.

In addition to self-reports of partners using strategies over time, we will ask each participant to test for HIV and STIs at baseline and at 6 months post baseline by going to a local community-based organization. Biological data for new diagnoses of HIV, chlamydia, gonorrhea, and syphilis will be collected. For those previously diagnosed with syphilis, the rapid plasma reagin test will be processed to examine antibodies to syphilis. HIV will be assessed using a rapid test, with a rapid test from another manufacturer used as a confirmatory test if the first is positive. GeneXpert polymerase chain reaction testing will be used to diagnose chlamydia and gonorrhea infections.

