#### Power, Sample Size, and Effect Size Estimations

All power calculations were performed with PASS 2020 [59]. For the couple-level analyses, with 60 couples randomized to 2 arms (30 couples in each), for outcome C, we will have 80% power to detect a difference of 0.75 SDs of the mean relationship functioning measure (large effect [60]) using a linear model. For the dichotomous outcomes A and B, we will have 80% power to detect an absolute difference of 35% between the intervention and delayed conditions using a chi-square test. Our power increases for the outcomes analyzed at the individual level, where the correlation between individuals within a dyad must be considered (ie, the interdependence of individuals nested within dyads). For the incidence rate of outcome D assuming Poisson distribution, 30 couples in each arm will have 80% power to detect a difference of 50% rate reduction in STI rate (including HIV) between the intervention and delayed conditions at 6 months assuming a within-pair coefficient of variation between clusters at 0.25 and the intraclass correlation coefficient as high as 0.1 (even higher ICCs do not reduce rate reduction measure in a significant or meaningful way magnitude wise). For all analyses, the α level was set at .05 with 95% CI. This is a feasibility and acceptability trial that is only powered to detect large effects; however, if effect sizes are lower than hypothesized, we will use that information to properly power a large-scale RCT.

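### HIV and STI tests are done only at baseline and month 6, so the 3-month analyses of outcome D cannot be run for tested infections, and the one available arm contrast compares 6 with 3 months of access

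*Protocol article*

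**What the plan says.** All references are to the protocol article.

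- **Testing schedule.** Trial Study Design: "participants will also undergo in-person HIV and STI testing at a local community-based organization at baseline and month 6". Pilot RCT Baseline and Follow-Up Measures repeats it: "we will ask each participant to test for HIV and STIs at baseline and at 6 months post baseline". Criterion 12 of the individual eligibility list asks for willingness to test at the same two times. No section schedules a month-3 test.
- **What outcome D contains.** Aim 3 states that "outcome D will be a count variable based on STI incidence, HIV incidence, and CAS". The Specific Aims describe it as "Self-reported and biomarker-confirmed indicators of vulnerability".
- **When the arms are compared.** Aim 3 places the comparison of "outcomes A to D by trial arm (immediate arm vs waitlist arm) will occur between baseline and month 3". The same paragraph plans, for A to D, the immediate arm's change at months 3 and 6, the waitlist arm's change from month 3 to month 6, and a pooled 3-month change over all 60 couples. Primary Analyses adds descriptive statistics for A to D at each time point, month 3 included.
- **Control exposure.** Under Randomization, the delayed condition is one where "couples will be able to use the P3 DHI for the last 3 months of the trial". That section places the between-arm comparison in the first 3 months.
- **Power.** The power section claims 80% power, with 30 couples per arm, for a 50% "rate reduction in STI rate (including HIV) between the intervention and delayed conditions at 6 months".

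**The concern.** An infection first detected at month 6 cannot be assigned to months 0-3 or months 3-6. Several analyses named for outcome D therefore have no data behind them where D means a study test result. The power section moves the infection comparison to month 6, a different time from the one given under Randomization and Aim 3, and at that time both arms have had access to P3.

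Two things are at stake. The biomarker part of the fourth efficacy outcome needs a defined contrast that can actually be estimated. And Aim 3 says the trial's effect estimates will be used to size a later efficacy trial. A month-6 infection ratio taken as the effect against no intervention would understate that effect whenever access works in both arms.

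**Working it through.** **Step 1. Match each planned analysis to the tests available.**

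| Planned for outcome D | Tests needed | Computable for tested infections? |
|---|---|---|
| Arm comparison, baseline to month 3 | 0 and 3 | No |
| Immediate arm, change 0-3 | 0 and 3 | No |
| Delayed arm, change 3-6 | 3 and 6 | No |
| Pooled 3-month change | 0, 3 and 6 | No |
| Month-3 descriptives | 3 | No |
| Immediate arm, change 0-6 | 0 and 6 | Yes |
| Arm comparison at month 6 | 0 and 6 | Yes, as 6 versus 3 months of access |

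Questionnaire measures are collected at baseline and months 3 and 6, so every row can be computed for self-reported CAS.

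**Step 2. Try to reproduce the stated power.** Inputs from the power section: 30 couples per arm, 50% reduction, coefficient of variation k = 0.25, alpha .05 (taken as two-sided). No control rate is given, so the 80% cannot be checked directly. One standard formula for comparing rates between clusters can instead be solved for the rate it implies:

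c = 1 + (1.960 + 0.842)² × [(m0 + m1) + k²(m0² + m1²)] / (m0 − m1)²

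Here m0 and m1 are infections per couple over 6 months. With c = 30 and m1 = 0.5 × m0, the solution is m0 = 1.77. Check at m0 = 1.774 and m1 = 0.887: the bracket is 2.661 + 0.0625 × 3.934 = 2.907, and 7.849 × 2.907 / 0.787 + 1 = 30. The pair-matched variant (2 in place of 1) gives 1.84. Two men followed for half a year make one person-year per couple, so this is about 177 to 184 infections per 100 person-years.

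**Step 3. Dilution at month 6 (illustration).** Assume P3 halves the rate as soon as access begins and the effect stays constant.

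- Immediate arm: 0.50 of the untreated rate.
- Delayed arm: (1 + 0.50)/2 = 0.75 of the untreated rate.
- Month-6 rate ratio: 0.50/0.75 = 0.67, a 33% reduction.

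In general, an on-access ratio r gives r / [(1 + r)/2] at month 6: r = 0.4 gives 0.57 and r = 0.7 gives 0.82. For a month-6 ratio of 0.50, r must be 1/3, an on-access reduction of about 67%.

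**Step 4. Power for the diluted contrast.** Power = Φ(|m0 − m1| × √[(c − 1)/((m0 + m1) + k²(m0² + m1²))] − 1.960). With delayed arm 0.75 × 1.774 = 1.3305 and immediate arm 0.887, the denominator is 2.2175 + 0.0625 × 2.557 = 2.377. Then 0.4435 × √(29/2.377) − 1.960 = −0.41, so power is 34%. The pair-matched variant at 1.84 also gives 34%.

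| Assumed untreated infections per couple, 6 months | 50% reduction, undiluted | Delayed arm with access in months 3-6 |
|---|---|---|
| 1.77 | 80% | 34% |
| 1.0 | 57% | 22% |
| 0.5 | 34% | 13% |
| 0.2 | 16% | 8% |

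The Results section reports 74 couples enrolled. If these split evenly (37 per arm, an assumption), the 34% becomes Φ(0.4435 × √(36/2.377) − 1.960) = Φ(−0.23), about 41%.

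**The case against.** A reader might infer that the month-6 comparison has no untreated control, or that infections have no intervention-versus-control comparison at all. The documents do not support that. The delayed arm has no access for the first 3 of the 6 months covered by the month-6 test, and infections acquired then count in its total. The contrast keeps its randomisation and is attenuated, not empty.

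It is also tempting to say that the power section treats the delayed arm as untreated. It does not say so. It names the delayed condition and gives a detectable difference at 6 months. Read literally, the 50% is the arm difference with crossover included. That reading is not an error in itself, but it is demanding, since it needs an on-access reduction of about 67% under the assumption above.

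Three further points stand. First, outcome D is not lost at month 3, because CAS is self-reported then. The item list is in Multimedia Appendix 1, which is not shown, so self-reported diagnoses may also be collected at month 3; the problem is established only for study-tested infections. Second, the 34% rests on a back-solved control rate and an assumed immediate, constant effect. The plan used PASS 2020 with inputs not fully stated, so the figure does not show that the plan's calculation is wrong. Third, this is a pilot that says it is powered only for large effects, and infection is one component of one of four efficacy outcomes.

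None of this supplies the missing month-3 test or removes the mismatch over when the arms are compared.

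**Conclusion.** The point holds for study-tested HIV, chlamydia, gonorrhea and syphilis. The month-3 arm comparison, the immediate arm's 0-3 month change, the delayed arm's 3-6 month change, the pooled 3-month change and the month-3 descriptives cannot be computed for them. This follows from the stated schedule and needs no assumption.

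The remaining between-arm contrast, at month 6, is a valid randomised comparison of 6 with 3 months of access. It is diluted relative to the untreated comparison that the plan describes for the first 3 months. How far it is diluted depends on assumptions: a true halving would appear as a rate ratio of about 0.67, and power would fall from 80% to about 34% at the implied control rate, or from 57% to 22% at 1.0 infection per couple. These figures show direction and scale and are not corrected values. Outcomes A, B and C and self-reported CAS keep their month-3 comparison.

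**What to change.** Data collection ended in April 2024, so the remedy lies in the analysis text and not in the testing schedule.

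1. **Aim 3 and Primary Analyses.** Limit the month-3 and 3-month analyses of outcome D, pooled and within-arm, to self-reported components such as CAS, and state that tested infections are exempt.
2. **Month-6 infection contrast.** Define it as immediate versus delayed access (6 versus 3 months) and report it with a confidence interval. It may be tested under that label. Do not interpret it, or carry it into future sample-size planning, as the effect against no intervention.
3. **Power section.** Delete the outcome D sentence, or restate it with the assumed control rate and a delayed arm that has access in months 3-6. If the 50% is kept, say that it is the diluted between-arm difference, equivalent to about a 67% on-access reduction if the effect is immediate and constant.

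The cost is wording and, if the power sentence is kept, one recalculation. The claim that can be made about tested infections becomes narrower.
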